### Statistical methods

All statistical analyses will be performed using SAS ver. 9.4 (SAS Institute Inc). Baseline characteristics will be summarized by group. Standardized mean differences (SMDs) will be used to assess baseline balance; variables with absolute SMD ≥ 0.25 will be considered imbalanced and included as covariates in sensitivity analyses.

Quantitative endpoints with repeated measures (HU, SNR, CNR, and MBF) will be analyzed using linear mixed-effects models with random intercepts for patients to account for intraindividual correlation across vessels or myocardial segments. Fixed effects will include contrast group, measurement location, and group × location interaction where appropriate. For the primary CCTA enhancement endpoint, noninferiority will be assessed using the estimated between-group difference (low minus high) and its two-sided 95% confidence interval. Noninferiority will be concluded if the lower bound of the 95% confidence interval for ΔHU is greater than –50 HU and if diagnostic adequacy criteria are met.

For the key secondary MBF endpoint, between-group differences will be estimated using a linear mixed-effects model. Because no clinically justified noninferiority or equivalence margin is prespecified for MBF, the analysis will be interpreted as an assessment of quantitative comparability rather than formal equivalence or noninferiority. A nonsignificant between-group difference will not be interpreted as proof of equivalence.

Qualitative image quality endpoints (Likert scores) will be compared using Mann–Whitney U-tests, with proportional-odds models as sensitivity analyses. Interobserver agreement will be assessed using weighted kappa for ordinal scales and Cohen κ for binary acceptability.

Exploratory diagnostic performance analyses will be conducted in the subset undergoing ICA and/or FFR. For CCTA using ICA as the reference standard, sensitivity, specificity, positive predictive value, and negative predictive value will be calculated for the detection of ≥ 50% coronary artery stenosis. Overall diagnostic performance will be quantified using receiver operating characteristic (ROC) curve analysis and the area under the ROC curve (AUC). For dynamic stress CTP versus FFR, similar metrics will be calculated for detecting FFR-defined ischemia (≤ 0.80). Because multiple vessels may be contributed by a single participant, analyses will account for within-patient clustering using methods such as generalized estimating equations for binary endpoints and cluster-robust variance estimators for AUC and confidence intervals. Prespecified sensitivity analyses will evaluate the impact of verification bias, as feasible given sample size. Missing data will be described and handled using appropriate methods for the endpoint, including mixed models under missing-at-random assumptions with sensitivity analyses if missingness is substantial.

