### Sample size

The sample size is based on the primary noninferiority endpoint for CCTA enhancement. Based on prior data indicating approximately a 10.77% reduction in ascending aortic attenuation with low- versus high-concentration contrast, the noninferiority margin is set at 11% (approximately 50 Hounsfield units [HU]) [14, 15]. Assuming a standard deviation (SD) of 119 HU, one-sided α = 0.025 and 90% power, 117 participants per group are required. Allowing for 10% attrition, the target enrollment is 129 participants per group (total, n = 258). Secondary MBF and exploratory diagnostic performance analyses will be interpreted in light of the available analyzable data and the number of participants undergoing clinically indicated invasive testing.

A formal pilot study was not performed, which may limit the precision of feasibility estimates before completion of the trial. However, the protocol was developed based on prior low-iodine CCTA studies and institutional experience with integrated CCTA and dynamic stress CTP, and recruitment feasibility will be monitored throughout the study period.

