### Randomization, allocation concealment, and blinding

Participants will be allocated 1:1 to the low- or high-concentration iodine contrast group using a computer-generated allocation protocol prepared by the Department of Preventive Medicine. The allocation sequence will be concealed from the principal investigator, research personnel involved in recruitment and endpoint assessment, participants, image readers, and outcome assessors. The principal investigator and research investigators will not know which contrast concentration is assigned at the time of patient enrollment, image analysis, or endpoint assessment. CT technologists involved in contrast preparation and injection may be aware of the assigned contrast media because the preparations differ; however, they will not participate in patient selection, randomization, image interpretation, endpoint assessment, statistical analysis, or clinical decision-making. After acquisition, CT images will be uploaded to PACS without visible contrast-group identifiers. The principal investigator, research investigators, image readers, and outcome assessors will analyze the anonymized imaging datasets in a blinded arrangement, and the final analytic dataset will be linked to the randomized allocation list only after blinded image analysis is complete. Participants will also not be informed of their assigned contrast concentration. Therefore, the study is described as participant-, investigator-, and reader-blinded, with transparent acknowledgement of technologist unblinding during contrast preparation.

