### Contrast media and injection protocols

Participants will receive either high-concentration iodine contrast media (iobitridol 350 mg I/mL; Xenetix 350, Guerbet) or low-concentration iodine contrast media (iohexol 270 mg I/mL; Iobrix 270, Taejoon Pharmaceutical). Dynamic stress CTP will use a fixed volume of 40 mL injected at 5 mL/sec followed by a 30 mL saline chaser in both groups. Therefore, under otherwise identical perfusion-acquisition conditions, the dynamic stress CTP analysis specifically tests whether iodine concentration affects quantitative MBF measurement and interpretability.

CCTA will use a triphasic protocol at 4.5 mL/sec: 0.9 mL/kg of the assigned contrast media, followed by 45 mL of a 70:30 saline-to-contrast mixture (70% saline and 30% contrast medium), and a final 30 mL saline chaser. Two intravenous lines will be secured for contrast media injection and adenosine triphosphate infusion. All injections will be performed with a dual-head power injector (Dual Shot GX7, Nemoto Kyorindo). Weight-based dosing and fixed scan timing are intended to standardize iodine delivery conditions across participants.

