### CT acquisition protocol

All examinations will be performed on a third-generation dual-source CT scanner (SOMATOM Force, Siemens Healthineers) and will comprise coronary calcium scoring, dynamic stress CTP, and CCTA (Fig. 2). For dynamic stress CTP, acquisition will begin 4 s after contrast initiation and proceed in shuttle mode (z-axis coverage 105 mm) over a fixed 32-s interval, yielding approximately 10 to 15 time frames depending on heart rate. Images will be acquired in end-systole using collimation of 96× 0.6 mm and rotation time of 250 ms. Tube voltage will be selected using automatic tube-voltage selection (CARE kV, Siemens Healthineers), and tube current will be modulated using CARE Dose4D (Siemens Healthineers), according to the same institutional cardiac CT protocol in both contrast groups. Physiologic data, including baseline heart rate, peak heart rate during CTP, and heart rate increment, will be recorded prospectively.

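### The primary HU model has no baseline covariate, and an SMD trigger selects covariates by chance imbalance; prespecifying body weight would gain modest precision at almost no cost

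*Protocol article*

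**What the plan says.** In the protocol article, Statistical methods, the repeated quantitative endpoints, including the primary HU endpoint, are analysed with a linear mixed model with a random patient intercept: "Fixed effects will include contrast group, measurement location, and group × location interaction where appropriate". No baseline covariate is named. The same section uses standardized mean differences to judge baseline balance. Variables at or above 0.25 in absolute value "will be considered imbalanced and included as covariates in sensitivity analyses". Adjustment therefore depends on the imbalance observed, and it stays outside the primary analysis.

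The Sample size section makes no allowance for adjustment: "Assuming a standard deviation (SD) of 119 HU, one-sided α = 0.025 and 90% power, 117 participants per group are required".

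Two other sections bear on whether weight could matter. Under Contrast media and injection protocols, the main CCTA bolus is 0.9 mL/kg, but "CCTA will use a triphasic protocol at 4.5 mL/sec" gives a rate that does not vary with weight, and the mixture phase is a fixed 45 mL. That section also says that dosing by weight and fixed timing are meant to even out iodine delivery between participants. Under CT acquisition protocol, tube voltage is selected automatically for each examination.

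**The concern.** A covariate improves precision in a randomized comparison because it predicts the outcome, not because it happens to differ between arms. The stated rule uses the second criterion. A strong predictor with an SMD of 0.24 stays out of every model, while an irrelevant variable with an SMD of 0.26 goes in. Which adjusted model will be reported is unknown until the baseline data are seen.

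Precision is what is at stake. Noninferiority requires the lower 95% confidence limit for the HU difference to lie above −50 HU (together with diagnostic adequacy). Any between-participant variance that a baseline variable could explain stays in the residual and widens that interval.

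**Working it through.** **Inputs.** From Sample size: margin 50 HU, SD 119 HU, one-sided α 0.025, power 90%, 117 per group. From Randomization: "Participants will be allocated 1:1 to the low- or high-concentration iodine contrast group". The true difference is not stated; zero is assumed because it reproduces the plan's figure. The SD is taken as that of a per-participant value. The within-arm correlation r between weight and that value is not in the documents; 0 to 0.5 is assumed.

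**1. The plan's own figure.** n per group = 2 × [119 × (1.960 + 1.282) / 50]² = 119.04, rounded up to 120, against 117 stated. At 117 per group, SE = 119 × √(2/117) = 15.6 HU and power = Φ(50/15.56 − 1.96) = 89.5%. A margin of 50.5 HU gives exactly 117, so the figure reproduces within rounding of the margin.

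**2. How often the trigger fires by chance.** SE(SMD) ≈ √(2/117) = 0.131, and 0.25/0.131 = 1.91, so P(|SMD| ≥ 0.25) = 5.6% per variable. At 129 per group it is 4.5%. The rule thus behaves much like a two-sided 5% test of baseline balance.

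**3. Whether weight is a plausible predictor.** The main bolus lasts 0.9/4.5 = 0.2 s per kg. At illustrative weights of 50 and 90 kg that is 10 s and 18 s. In the 350 mg I/mL arm the iodine delivery rate is 4.5 × 350 = 1575 mg I/s, or 31.5 mg I/s per kg at 50 kg and 17.5 at 90 kg. Scaling the volume therefore does not scale the rate of delivery. The bolus-tracking threshold and delay are the same for everyone. A residual weight–HU relation is plausible, but the documents do not show its size.

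**4. What adjustment would gain.** Residual SD = 119 × √(1 − r²), put back into the formulas of step 1 (the one degree of freedom used is ignored):

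| Assumed r | Residual SD (HU) | Power at 117 per group | 95% CI half-width (HU) | n per group for 90% power |
|---|---|---|---|---|
| 0 | 119.0 | 89.5% | 30.5 | 120 |
| 0.2 | 116.6 | 90.7% | 29.9 | 115 |
| 0.3 | 113.5 | 92.1% | 29.1 | 109 |
| 0.4 | 109.1 | 93.9% | 27.9 | 100 |
| 0.5 | 103.1 | 96.0% | 26.4 | 90 |

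If the low-concentration arm truly lost 10 HU (illustrative), power would be Φ(40/15.56 − 1.96) = 72.9% unadjusted, 76.9% at r = 0.3 and 84.3% at r = 0.5.

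**5. Chance shift left by an imbalance just under the trigger.** Shift ≈ SMD × r × 119. At SMD 0.25 this is 8.9 HU for r = 0.3 and 14.9 HU for r = 0.5. At the average chance imbalance, 0.131 × √(2/π) ≈ 0.10, and r = 0.3, it is about 4 HU.

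**The case against.** The strongest reply is that nothing in the plan is statistically wrong, and that stands. Allocation is randomized, so the unadjusted difference is unbiased over randomizations and type I error is not inflated. The sample size uses the unadjusted SD, so planned power of about 90% does not depend on adjustment. An optional gain is left untaken; nothing promised is lost.

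The article is also a condensed text, and a covariate list is often left to the analysis plan, which is not shown. The verb in the fixed-effects sentence could be read as non-exhaustive. That carries some weight. But the article does state both the model terms and the rule by which covariates enter, and it places them in sensitivity analyses. The criticism is of that stated rule.

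A reader might infer more than the documents support:

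- That body weight drives HU. No section says so or gives a correlation, and the 0.9 mL/kg bolus is meant to weaken that dependence. The unscaled rate and mixture phase make a residual relation plausible, no more.
- That an imbalance below 0.25 biases the result. It is chance error in either direction, already covered by the confidence interval. Even the near-worst case of 14.9 HU is about one SE (15.6 HU).
- That the primary result depends on a model chosen from the data. The primary model is fixed in advance; only a sensitivity model varies, under a numeric rule set beforehand.
- That baseline heart rate belongs in the primary model too. The article says "Physiologic data, including baseline heart rate, peak heart rate during CTP, and heart rate increment, will be recorded prospectively" but nowhere links heart rate to coronary HU.

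**Conclusion.** The point holds as a modest matter of efficiency and prespecification. As stated, the primary HU model carries no baseline covariate, and the only route to adjustment is a trigger unrelated to prognosis. How much precision is forgone depends wholly on r. There is no gain at r = 0, about 1 to 3 power points and a half-width 0.6 to 1.4 HU narrower at r = 0.2 to 0.3, and 6.5 points and 4.1 HU at r = 0.5. These figures assume 117 evaluable participants per group, zero true difference and an SD of 119 HU. It is not an error in the primary analysis, and the planned noninferiority test remains valid if nothing is changed. The calculation covers the HU endpoint only and was not extended to MBF.

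**What to change.** Before unblinding, that is, before the analytic dataset is linked to the allocation list, amend Statistical methods in four respects:

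- Add body weight, as a continuous fixed effect, to the primary HU mixed model.
- Report the model without weight as a sensitivity analysis.
- Delete the 0.25 SMD trigger and keep SMDs as a descriptive summary of baseline balance.
- Keep selected tube voltage out of the primary model, because it is set at the scan, after randomization.

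The cost is a sentence or two of wording and one model degree of freedom. No new data are needed, since weight is already required to calculate the bolus. Made after unblinding, the same change would look data-driven.

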### CT reconstruction and post-processing

Dynamic stress CTP datasets will be reconstructed in the axial plane (slice thickness 3 mm, 2 mm overlap) using a medium-sharp quantitative kernel (Qr40, Siemens Healthineers) to preserve linearity of iodine attenuation. Post-processing will be performed on a workstation (Syngo.via VB10, Siemens Healthineers) using commercial perfusion software. MBF (milliliters per 100 mL/min) will be derived by parametric deconvolution based on a two-compartment tracer-kinetic model applied to time-attenuation curves. The arterial input function will be placed in the ascending aorta or left ventricular cavity using standardized regions of interest (ROIs). The left ventricle will be segmented according to the American Heart Association (AHA) 17-segment model and polar maps generated for territorial and segmental analyses.

CCTA datasets will be reconstructed with a medium-soft vascular kernel (Bv40, Siemens Healthineers) and iterative reconstruction (ADMIRE strength 3, Siemens Healthineers). Images will be transferred to an offline workstation for post-processing, and optimal phases (mid-diastolic and/or end-systolic) will be selected for evaluation. Dynamic stress CTP and CCTA acquisition parameters, including tube-voltage strategy, ECG-gating approach, reconstruction kernel, slice thickness, and iterative reconstruction settings, will be applied identically in both contrast groups to support reproducibility and minimize confounding by scan parameters.

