### Image analysis

Quantitative CCTA image quality will be evaluated using ROIs in proximal and distal segments of each major coronary artery (left anterior descending coronary artery, left circumflex artery, right coronary artery) to obtain mean attenuation (HU) (Fig. 3A–C). Image noise will be defined as the SD of attenuation in a homogeneous ascending aortic ROI (Fig. 3D). Signal to noise ratio (SNR) and contrast to noise ratio (CNR) will be calculated as SNR = HU_coronary_/SD_aorta_ and CNR = (HU_coronary_ – HU_myocardium_)/SD_aorta_, where HU_myocardium_ is measured from a mid-ventricular septal ROI (Fig. 3E). Measurements will be performed on the optimal phase and averaged for per-vessel and per-patient analyses.

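### A patient random intercept alone treats all sites and segments in a patient as equally correlated, so some group × location contrasts may have wrong standard errors; the primary comparison is not affected

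*Protocol article*

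**What the plan says.** Statistical methods in the protocol article sets one model family for all repeated quantitative endpoints: "linear mixed-effects models with random intercepts for patients to account for intraindividual correlation across vessels or myocardial segments". It continues: "Fixed effects will include contrast group, measurement location, and group × location interaction where appropriate". No vessel-level or territory-level random effect, other residual covariance or robust variance is named for these endpoints. Cluster-robust methods appear only for the exploratory diagnostic-performance analyses.

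The locations have structure. Image analysis places "ROIs in proximal and distal segments of each major coronary artery", which makes six sites in three vessels. It also says that the measurements are "averaged for per-vessel and per-patient analyses". For MBF there are 17 segments, with "polar maps generated for territorial and segmental analyses" (CT reconstruction and post-processing). The main MBF analysis keeps all analyzable segments, ischemic ones included.

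The primary decision rests on the overall group difference: "Noninferiority will be concluded if the lower bound of the 95% confidence interval for ΔHU is greater than" minus 50 HU, together with diagnostic adequacy. MBF has no margin. No decision is attached to the interaction.

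**The concern.** A patient intercept accounts for within-patient correlation only if any two locations in a patient are equally correlated. In known or suspected coronary disease, a stenosis tends to lower MBF across its whole territory, so segments of one territory should resemble each other more than segments of another. Patients may also differ in how far attenuation falls from proximal to distal, and sites in one vessel may share features.

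The model would then use one pooled within-patient residual for contrasts whose true errors differ. The questions at risk are regional: whether low iodine changes MBF in some territories, or loses more attenuation distally. A false regional signal could be reported as an effect of the contrast medium, or a real distal loss could be missed.

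**Working it through.** **The plan's own figure.** Sample size states: "Assuming a standard deviation (SD) of 119 HU, one-sided α = 0.025 and 90% power". With a 50 HU margin and no true difference, n = 2 × (1.960 + 1.282)² × 119² / 50² = 119.04, so 120 per arm. The article states 117, which a margin of 50.5 HU reproduces; power at 117 is 89.5%. The figures agree within 3%. They concern the overall comparison, which this point leaves alone.

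**Inputs.** 117 per arm; 17 segments; six coronary sites (all from the article). Assumed, because the article gives no figures: a 7/5/5 split of segments over three territories, and the variance ratios below. Residual variance at one location is set to 1. There is no true interaction, data are complete, and the nominal level is 5%.

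**Group × territory, MBF.** Let r be the between-territory variance within a patient, relative to the residual.
- Pooled residual used by the model: e = 1 + r × (17 − 99/17)/16 = 1 + 0.70r, where 99 = 7² + 5² + 5².
- With 17/3 = 5.67 segments per territory on average, the true variance of a territory deviation is proportional to r + 1/5.67. The model assumes e/5.67.
- Ratio of true to assumed variance: R = (1 + 5.67r)/(1 + 0.70r).
- Rejection of the 2-df test: exp(−2.996/R).

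| r | R | formula | simulated |
|---|---|---|---|
| 0.05 | 1.24 | 8.9% | 8–9% |
| 0.11 | 1.51 | 13.7% | 13–14% |
| 0.25 | 2.06 | 23.3% | 21–23% |
| 0.5 | 2.84 | 34.8% | 34–35% |
| 1 | 3.92 | 46.6% | 47–48% |

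A REML mixed-model fit at r = 0.25 (150 replicates) gave 24%.

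**Group × proximal/distal, HU.** Let g be the variance of the patient-specific proximal-minus-distal difference and q the between-vessel variance within a patient, both relative to the residual.
- The contrast of three proximal with three distal sites has true variance g + 2/3. Vessel effects cancel.
- The model assumes (2/3) × (1 + 0.3g + 0.8q).
- R = (1 + 1.5g)/(1 + 0.3g + 0.8q); rejection = 2 × [1 − Φ(1.96/√R)].

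| g | q | R | rejection |
|---|---|---|---|
| 0.25 | 0 | 1.28 | 8.3% |
| 0.5 | 0 | 1.52 | 11.2% |
| 1 | 0 | 1.92 | about 16% |
| 0.5 | 0.5 | 1.13 | 6.5% |
| 0 | 0.5 | 0.71 | 2.0% |

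Simulation agrees: 9%, 12% and 15% for the first three rows, and 2.2% for vessel clustering alone at q = 0.43. More extreme values widen the range (about 22% at g = 2, about 1% at q = 1).

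**Omnibus tests.** The 16-df group × segment test rejects about 5–11% over the same range of r. The 5-df group × site test rejects about 5–6% over the tabulated g and q.

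**Overall group effect.** With complete data it compares patient means, so the division of within-patient variance does not enter. Simulated rejection was 5.0–5.1%. With territories dropped at random it was 4.5% and 5.3%.

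**After the correction.** When each contrast is tested against its own patient-level error, rejection returns to 5.0–5.4% for territories and 4.7–5.3% for proximal versus distal.

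**The case against.** The strongest reply is that the article names no group × territory or group × proximal/distal test. The interaction enters only where appropriate, the wording about territorial analyses describes polar-map output, and distal visualization is also judged by readers. If location means the 17 segments or the six sites, the test nearest the text is the omnibus one, which is close to nominal. If vessel averages enter the HU model, no proximal/distal contrast exists. Covariance details are commonly left to the analysis plan, and the article does not say that the patient intercept is the only random effect.

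Most of this stands and limits the point. What remains is that the article names the patient intercept as the device that handles correlation across vessels and segments. Used alone, it does so only under equal correlation, and any regional contrast or interval drawn from such a model inherits the problem.

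A reader might go further and infer that the noninferiority conclusion is at risk, or that interaction tests in general reject several times too often. The documents support neither. The decision rule uses the overall difference, which keeps its size. Large inflation arises for territory contrasts under assumed variances; omnibus tests barely move, and proximal/distal contrasts can err towards caution.

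**Conclusion.** The concern holds in a limited form. Used alone, the stated patient intercept gives wrong standard errors for structured location contrasts whenever vessels, territories or the proximal-to-distal gradient add their own within-patient variance. The clearest case is group × territory for MBF, where a ratio of only 0.11 already gives about 14%. For proximal versus distal HU even the direction of the error is unknown.

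These sizes rest on assumed variance ratios, an assumed 7/5/5 segment split and complete data, and nothing in the article shows which end of the range applies. The primary ΔHU test, the overall MBF difference and the sample size are unchanged. Minor priority.

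**What to change.** Keep the stated model for the primary ΔHU estimate; an unstructured covariance there is not needed. For every group × location test and location-specific interval, do one of the following:
- use empirical (sandwich) standard errors clustered on patient; or
- add a territory-within-patient random effect for MBF, and vessel-within-patient and patient-level proximal/distal effects for HU.

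The text should also say what location means for each endpoint (segment or territory; site or vessel average), since that determines how much the choice matters.

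The cost is one sentence in the statistical section and a few lines of SAS. Intervals for some location-specific contrasts will be somewhat wider. Sandwich errors correct the standard errors but leave the estimates as they are, so the nested random effects are the better choice if many segments are missing.
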